#### Staff experience interview

Semistructured interviews will be conducted with up to 15 (or until saturation in the data is reached) healthcare staff who were responsible for monitoring the data and interacting with patients with COVID-19 for a minimum of at least 1 week at the clinic and agree to take part in the study. These interviews will be conducted by trained interviewers and will take approximately 30 min. Interviews will be conducted over the phone and recorded using audio-recorder or via video call on Zoom and the video call recorded. A topic guide was developed to explore the staff member’s experience of the remote monitoring process, including their role in the clinic; the usefulness of equipment such as pulse oximeters; how well the equipment was received by patients; their experiences of the remote monitoring intervention compared with treatment-as-usual, such as interactions with patients; the impact of remote monitoring on reducing the burden placed on healthcare staff during the pandemic; the benefits and drawback of using remote monitoring; how remote monitoring can be improved and their opinions on using remote monitoring for other types of conditions.

### Data analysis: work package 2

To achieve the second objective of this project, the data collected during the qualitative interviews with the healthcare staff members will be analysed. These interviews will be transcribed verbatim, and a thematic analysis will be conducted using NVivo to identify common themes throughout the interviews. An inductive approach will be taken to draw out themes by one researcher and will then be reviewed by the research team to ensure that all emerging topics are included, following the same steps as work package 1. A secondary researcher will independently code a subset of transcripts to assess the internal reliability.

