Recent evidence, although limited, suggests healthcare staff generally have positive experiences with the use of telemedicine during the COVID-19 pandemic and that it may play an important role in their well-being.^42 43^ For example, healthcare staff reported that they felt that the technology was easy to use and were satisfied with the safety precautions implemented to allow them to work from home.^42^ Research indicates that healthcare staff generally hold positive views towards the remote monitoring of patients across numerous conditions.^44^ However, there are notable concerns, such as managing increased workload and reduced quality of care from fewer patient visits.^44 45^ This suggests that further research is required to better understand the staff experience of remote monitoring technology for patients with COVID-19, particularly across a diverse range of healthcare roles.

This project aims to evaluate a remote monitoring intervention for managing COVID-19 cases in a large urban teaching hospital in Dublin, Ireland. The objectives of this project are twofold. First, the acceptance of the remote monitoring technology from the perspective of the patient (objective 1a) and healthcare staff (objective 1b) will be examined using a mixed methods approach. User acceptance from the perspective of the patient will be examined using factors extracted from an integrated model of the UTAUT and TTF models,^33^ while also controlling for a number of covariates, using quantitative analyses. User acceptance of remote monitoring for managing patients with COVID-19 from the perspective of both the patient and healthcare staff will also be examined using a qualitative methodology.

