## Methods

### Research design

A mixed methods design is proposed to achieve the research objectives of this project. The measures used to collect the data consist of both quantitative measures (eg, user acceptance of the remote monitoring technology) and qualitative interviews (for both patient and staff experience of remote monitoring). Work package 1 will use both quantitative cross-sectional survey data and qualitive interviews to examine patient experiences. Work package 1 will address objectives 1a and 2. Quantitative analyses will be used to determine the acceptance of the remote monitoring technology among the patients and to identify the patient symptom profiles of COVID-19 and postacute COVID-19. Work package 2 will use qualitative interviews to examine healthcare staff experiences. Work package 2 will address objective 1b.

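### One staff interview topic asks only about reduced burden, although the protocol itself names increased workload as a known staff concern

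*Protocol article*

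**What the plan says.** The Introduction sets objective 1b as acceptance of the remote monitoring technology from the perspective of healthcare staff, and objective 2 as patient symptom profiles identified by quantitative methods. It describes staff views of remote monitoring as generally positive, but records concerns about "managing increased workload and reduced quality of care from fewer patient visits".

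Under Research design, the mapping is explicit: "Work package 2 will address objective 1b", while work package 1 takes objectives 1a and 2. Work package 2 consists of semistructured interviews with up to 15 staff, about 30 minutes each. There is no staff survey.

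The section Staff experience interview summarises the guide: "A topic guide was developed to explore the staff member’s experience of the remote monitoring process, including their role in the clinic". Equipment is covered next, both its usefulness and its reception by patients, and then a comparison with treatment-as-usual. The topic at issue here is "the impact of remote monitoring on reducing the burden placed on healthcare staff during the pandemic". A further entry leaves staff room to raise negative experience and suggest changes: "the benefits and drawback of using remote monitoring; how remote monitoring can be improved". The last one asks for views on extending the approach to other conditions.

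Data analysis: work package 2 then opens with "To achieve the second objective of this project" and describes an inductive thematic analysis that follows the steps of work package 1. Those steps call for themes not drawn from existing theory or from what the researchers already believe.

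**The concern.** The burden topic names relief as the thing to be discussed. A staff member whose workload rose, or moved from bedside to telephone and data review, is not invited by that wording to say so. Yet increased workload is one of the two staff concerns that the protocol picks out from the literature. The Abstract gives reduced burden on healthcare systems as a reason why remote monitoring was introduced, so the topic repeats part of the rationale for the service under evaluation.

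At stake is the balance of what staff report on workload. Inductive coding can only work on what was said. If the prompt tilts the answers, careful coding and a second coder will not restore what was not raised. No other data source for objective 1b could show the tilt.

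Separately, the analysis section ties these interviews to an objective that they cannot serve.

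**Working it through.** No arithmetic applies; the check is a comparison of the text.

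**Direction of the burden topic**

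| Place | Content | Direction |
|---|---|---|
| Introduction, staff evidence | Increased workload and reduced quality of care named as concerns | Adverse |
| Staff experience interview, burden topic | Impact on reducing burden | Favourable only |
| Staff experience interview, comparison topic | Experience against treatment-as-usual, including interactions with patients | Neutral |
| Staff experience interview, later topics | Benefits and drawbacks; improvements | Both |
| Patient experience interview, comparison topic | Opinion against treatment-as-usual | Neutral |

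Only the burden topic presumes a direction, and it is the opposite of the workload concern in the Introduction. The comparison topics in both guides show that neutral phrasing was available.

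**How much of the guide is affected**

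The listed staff topics are:

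1. role in the clinic
2. usefulness of equipment
3. how patients received it
4. comparison with treatment-as-usual
5. burden
6. benefits and drawbacks
7. improvements
8. use in other conditions

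One of the eight is directional. Topics 6 and 7 open the door to negative experience. Topic 4 bears on quality of care, because the Introduction links that concern to fewer patient visits.

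**Objective label**

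- Introduction: objective 1b is staff acceptance; objective 2 is patient symptom profiles, quantitative.
- Research design: work package 2 serves objective 1b; work package 1 serves 1a and 2.
- Data analysis: work package 2: the staff interviews serve the second objective.

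The third statement contradicts the other two, since qualitative staff interviews cannot yield quantitative patient symptom profiles. The likely source is that the analysis sections number objectives by work package: the work package 1 analysis opens with the first objective and runs on to the latent class analysis. This is an inference, and the correction does not depend on it.

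**The case against.** The strongest reply is that the article paraphrases the guide. The quoted phrase is a topic label, and the question actually put to staff is not shown. The interviews are semistructured and led by trained interviewers, who can follow up. Drawbacks and improvements come next in the same sentence. Themes are reviewed by the research team, and a second researcher codes a subset of transcripts. No steering of the themes has been demonstrated.

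Most of this stands, and it limits the size of the point. It does not remove it: the label is the only wording that the protocol commits to, and it departs from the protocol's own evidence.

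Two stronger readings are tempting, and the document supports neither.

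- *That acceptance topics are missing.* The list does not name staff's own ease of use, training and resources, or willingness to continue. However, it is introduced as a partial list, and an article commonly leaves the full guide to other documents. Usefulness, comparison with usual care, improvements and wider use already bear on acceptance. Nor does the protocol plan a factor-by-factor comparison of staff with patients: it applies the technology-acceptance factors to the patient survey, and the interview coding is inductive.
- *That objective 1b will be answered poorly or one-sidedly.* The benefits-and-drawbacks topic contradicts this directly. The wrong label cannot support it either, because relabelling changes no participant, question or analysis.

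**Conclusion.** The point holds in a narrow form: one of eight listed staff topics is worded in a single direction, against a workload concern that the protocol itself cites, in the only data source for objective 1b. The expected effect is modest and cannot be quantified from the document, given the offsetting topics and the semistructured format. The conclusion assumes that the article's wording is close to the wording of the guide. If the guide already asks about workload neutrally, only the summary needs editing.

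The objective label is a definite contradiction, but a clerical one, since Research design states the correct mapping. Taken together, this is an inexpensive improvement and not a defect that puts objective 1b at risk.

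**What to change.** - In Staff experience interview, and in the topic guide if it carries the same wording, replace the burden topic with a neutral one, for example: *the effect of remote monitoring on staff workload and burden, whether increased, reduced or shifted*.
- In Data analysis: work package 2, replace the reference to the second objective with objective 1b, to agree with the Introduction and Research design.

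The cost is an edit of two phrases. It adds no participants, interview time or analysis. If some interviews have already been held, note which ones used the directional wording, so that workload themes can be read with that in mind.

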### Patient and public involvement

Patients and/or the public were not involved in the design of this study protocol.

### Ethics and dissemination

Ethical approval has been granted by the National Research Ethics Committee for COVID-19-related Research (NREC COVID-19; reference number: 20-NREC-COV-093). Data sharing agreements have been put in place between the University College Dublin (UCD) research team and the hospital. The data will be deidentified and securely transferred to the research team, in accordance with data protection regulations. No identifiable data will be included in the data set received by the research team at UCD. Online consent will be obtained from the participants of this project.

Findings will be disseminated via publications in scientific journals, policy briefs, short reports and social media. A summary of the findings will also be shared with participants who informed the research team that they are interested in the results of the project.
